**Hypothesis 2**
1. Time of emergent intubation post-ICU transfer (emergent is defined by clinician’s notes as a nonplanned procedure)2. Time of the first order post-ICU transfer for transfusion of 3 units or more of blood ordered within 24 hours3. Time of first order post-ICU transfer of intravenous inotropes or pressors administered for shock (including septic shock)4. Time of cardiac arrest post-ICU transfer5. Time of congestive heart failure escalation, defined by the time of first order for diuretic drip, time of first order for continuous venovenous hemodialysis, or time of dialysis initiation6. Time of death post-ICU transfer7. “Infinite” event-free survival, defined as discharge from the ICU without an event
**Hypotheses 3 and 4**
1. Time to the first order for transfusion of 3 units or more of blood ordered within 24 hours2. Time to first order for blood or urine culture obtained for suspicion of infection3. Time to first order for lactate drawn4. Time to first order for anti-infectives given for suspicion of infection5. Time to first order for fluid resuscitation given for suspicion of shock6. Time to rapid response team medical emergency team call initiation7. Time to first order for intravenous inotropes or vasopressors administered

#### Secondary Hypothesis

The secondary hypothesis is that display of predictive analytics monitoring on acute care cardiology wards increases the number of hours free of clinical deterioration among those emergently transferred to the ICU.

We will use the Kaplan-Meier method or Cox proportional hazards regression curve to show post-ICU transfer event-free survival and hours free of the events listed in Textbox 1. The analysis comparison will employ a 1-sided clustered log-rank test (survival analysis) assuming proportional hazard rates.

For secondary outcomes measured as proportions (ie, yes-or-no outcomes) we will use GEEs with logit link and binomial distribution, and use negative binomial distribution for rare events. GEEs will allow the correct modeling of the clustering design and estimation of the intracluster correlation.

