### Randomization Process

The room and bed in which a patient is placed is based on standard of care. The rooms are being cluster randomized to either intervention or usual care. The assignment of patients to rooms will not be influenced by the randomization status of the room.

There will be 14 clusters containing an average of 4 rooms (6 beds) each, with the aim of maintaining balance across wards and units (intermediate care unit, transplant, or neither). Clusters will be rerandomized every 2 months following a replicated Latin square design within each stratum to ensure balanced treatment assignment within each time period and over the length of the study. Randomization will be performed using the randomization inference package in R (The R Foundation for Statistical Computing). The randomization will be masked until it is implemented every 2 months. Postimplementation, the randomization will not masked or blinded because it will be clear to anyone in the hall or central station which beds have a CoMET score displayed and which do not. Future randomization assignments will only be known by the study statistician (SR) and those technical personnel implementing CoMET at the time that randomization changes (MC).

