### Implementation and Education Considerations for Clinicians

All clinicians will be educated about CoMET to follow assessment guidelines in response to CoMET score. With consideration to alert fatigue, an increase of 2 or more within a period of 3 hours was selected as a guideline for assessment. In our retrospective cohort, a rise >2 units occurs 2 to 3 times per ward per day. On average then, a single nurse may experience 1 CoMET rise alert every 3 shifts. The clinicians will be provided education about what a score rising on either (or both) axes represents and the differential diagnoses to consider. This approach leaves the clinical context to that of the clinician and does not specify the specific diagnostics to order. The purpose of CoMET is to alert clinicians to prodromes or subtle physiological changes that precede overt clinical signs and draw attention to patients who may be in need of further attention, further clinical diagnostics, or escalation in care delivery. Clinicians may choose to draw a blood culture, initiate a rapid response team call, initiate oxygen therapy, or to do nothing but closely monitor or reassess the patient in an hour. Because CoMET models are trained on multiple events of clinical deterioration, clinicians understand the context of the CoMET score within the larger patient trajectory. There will be continual engagement and re-education throughout the entire study period across all clinician groups.

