**Hypotheses 2 and 4**
1. Proportions of the following individual events at any point in the hospital stay after admission to the fourth floor:Emergent ICU transfer (emergent defined as urgent, unplanned)Emergent intubation (emergent is defined by clinician’s notes as a nonplanned procedure)3 units or more of blood ordered in 24 hoursinotropes or vasopressor useShock requiring inotropes or vasopressorsSepsis (sepsis-2 definition)Septic shock requiring inotropes or pressors (defined by a combination of the 2 above criteria)Cardiac arrestDeathDiuretic drip indicating congestive heart failure escalationInotropes or pressors for heart failureEmergent surgery prior to ICU transfer (emergent is defined by clinician’s notes as a nonplanned procedure)2. Hospital length of stay3. In patients who are never transferred to the ICU, the length of stay on the acute care floor4. ICU length of stay5. Proportion with readmission to hospital within 72 hours postdischarge6. In patients who meet the sepsis-2 criteria, the proportion of shock (ie, hypotension requiring inotropes or pressors), and death7. Number of days on intravenous antibiotics8. Number of days on intravenous anti-infectives9. Total duration of mechanical intubation (emergent and nonemergent)10. Impact of sex on outcome

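### The secondary log-rank test compares arms only among emergently transferred patients, a group the display is meant to change, and it is 1-sided with no stated level

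*Protocol article*

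**What the plan says.** The Secondary Hypothesis section states that the display "increases the number of hours free of clinical deterioration among those emergently transferred to the ICU". Kaplan-Meier or Cox curves are to be used "to show post-ICU transfer event-free survival and hours free of the events listed in Textbox 1". The test is named: "The analysis comparison will employ a 1-sided clustered log-rank test (survival analysis) assuming proportional hazard rates". No significance level is attached to it.

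Textbox 1, under Hypothesis 2, times most of the events from ICU transfer and assigns infinite event-free survival to "discharge from the ICU without an event".

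Three other parts of the article bear on this:

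- Textbox 1, Hypothesis 1, makes emergent ICU transfer a component of the primary outcome.
- Implementation and Education Considerations for Clinicians says the display should "draw attention to patients who may be in need of further attention, further clinical diagnostics, or escalation in care delivery".
- Randomization Process says that once an assignment is in place "it will be clear to anyone in the hall or central station which beds have a CoMET score displayed".

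Textbox 1, under Hypotheses 2 and 4, contains two more outcomes restricted by what happens after randomization: "In patients who meet the sepsis-2 criteria, the proportion of shock" and death, and "In patients who are never transferred to the ICU, the length of stay on the acute care floor". The same list also holds outcomes for all admissions: whole-stay proportions with ICU transfer, intubation, septic shock, arrest and death, and hospital length of stay. The proportions are analysed by GEE, with no sidedness stated.

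The commitment to analyse all randomized participants is made for the primary end point only.

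**The concern.** Randomization makes the arms comparable at admission to a study room. It does not make the transferred patients comparable, because transfer is decided later, by staff who can see the display, and the display is there to influence such decisions. If the trial's own primary hypothesis is true, the two transferred groups differ in make-up.

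The error can run either way:

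- If the display leads to more transfers of less ill patients, event-free survival after transfer improves in that arm although nobody's course has changed. Each such patient who leaves the ICU without an event is scored as the best possible outcome.
- If the display averts the mildest transfers, the remaining group is sicker and the display looks worse although it helped.

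Starting the clock at transfer adds a lead-time effect. The same patient with the same event at the same moment gains event-free hours by being transferred sooner.

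Sidedness is a separate fault. A 1-sided test for benefit has no rejection region for harm, and without a stated level the strength of evidence required is unknown. At stake is whether the secondary result can be interpreted. The primary analysis is not affected.

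**Working it through.** The article states no event count, effect size, level or power for this test, so there is no figure to reproduce.

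**Inputs from the article.** 10,424 admissions; 11% lost from the primary outcome; overall type I error 5% with sides not stated; nominal levels .003 (interim) and .047 (final). 10,424 × 0.89 = 9,277, or about 4,639 per arm if split equally.

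**Assumed, because the article gives no value.** Transfer rate, risk of an event after transfer, and how strongly that risk depends on severity at transfer.

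**Step 1: hand calculation.** Assume 5% of usual-care patients are transferred (232) and 40% of them have an event.

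- Display adds 20% more transfers (278 in all) at 10% risk, with no effect on anyone. Event rate (5 × 0.40 + 1 × 0.10)/6 = 35.0%. SE = √(0.40 × 0.60/232 + 0.35 × 0.65/278) = 0.043, so expected z = 0.05/0.043 = 1.16. Chance of declaring benefit: P(Z > 1.645 − 1.16) = 0.31 at 1-sided 5%; P(Z > 1.96 − 1.16) = 0.21 at 1-sided 2.5% or 2-sided 5%.
- Display averts the mildest 20% (10% risk). Event rate among the remaining 186: (5 × 0.40 − 1 × 0.10)/4 = 47.5%, against 40%. SE = √(0.475 × 0.525/186 + 0.40 × 0.60/232) = 0.049; expected z about 1.5 in the direction of harm.

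**Step 2: simulation of the log-rank test.** 9,277 patients split 1:1, 1,000 runs per setting, clustering ignored. Severity s is standard normal, and patients above a threshold are transferred. The post-transfer hazard per hour is (1/400) × exp[β(s − 1.645)], the same in both arms, with follow-up cut at 504 h. The display only moves the transfer threshold. The table shows how often the test crosses 1.645 in the stated direction.

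| Usual-care transfer rate | β | 20% more transfers: false benefit | 40% more: false benefit | 20% fewer: looks worse |
|---|---|---|---|---|
| 3% | 0.5 / 1.0 / 1.5 | 6.7 / 12.9 / 21.5% | 14.0 / 29.1 / 45.7% | 8.6 / 14.4 / 23.8% |
| 5% | 0.5 / 1.0 / 1.5 | 8.8 / 17.7 / 31.2% | 18.0 / 41.9 / 66.9% | 9.3 / 20.8 / 30.9% |
| 8% | 0.5 / 1.0 / 1.5 | 11.8 / 25.0 / 40.7% | 23.4 / 56.7 / 84.9% | 13.6 / 30.3 / 44.4% |

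With the same threshold in both arms, the false-benefit rate is 4.5–6.0%, as intended. With 20% fewer transfers, benefit is declared in only 0–1.9% of runs.

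**Step 3: lead time alone.** Transfer rate 5%, β = 1.0, same patients and same event times, but display-arm patients transferred earlier. The false-benefit rate is 7.8% for 6 h and 12.5% for 12 h.

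**Step 4: sidedness.** For a Lan-DeMets O'Brien-Fleming spending function at half the information, 0.025 per side, the amount spent per side is 2[1 − Φ(2.241/√0.5)] = 0.0015. Doubled, this is .003, the stated interim value. A 1-sided 5% design would give 0.0056. The primary therefore looks like a 2-sided 5% design.

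For a true hazard ratio of 1.33 (harm) and 300 events, the expected z is √(300/4) × ln(1/0.75) = 2.49. A 2-sided 5% test flags harm with probability P(Z > 1.96 − 2.49) = 0.70 (0.53 at 200 events, 0.30 at 100). The 1-sided 5% benefit test rejects with probability P(Z > 1.645 + 2.49), about 0.00002.

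**The case against.** The strongest reply is that Hypothesis 2 does not rest on this test alone. Textbox 1 lists whole-stay proportions under the same hypothesis, unrestricted by transfer and analysed by GEE without a 1-sided label. A reader might infer that every secondary outcome is confined to transferred patients, or that the trial is blind to harm. The document supports neither. The restriction applies to the hypothesis as worded and to its log-rank test. Harm could still appear in the curves, in those proportions, and in the primary outcome, where a death scores 0 hours. This reply narrows the point but does not remove it, because the named test remains the one described above.

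A second objection is that a 1-sided test loses nothing when averted mild transfers make the display look worse, since that signal is false. This is right. Making the subset test 2-sided would only make false harm easier to declare. Sidedness therefore has to be corrected together with the population.

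A third is that the sepsis-2 and never-transferred outcomes stand beside all-admission counterparts, and that a shift toward milder sepsis through more cultures is conjecture, given coordinator review of suspected infection. This stands: those outcomes share the structure of the problem but carry less weight.

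**Conclusion.** The point holds for the named log-rank test. It conditions on a post-randomization event that belongs to the primary outcome and that the display is meant to change. It counts time from that event, and it is 1-sided with no level given. A significant result would not show that the display improves the course after transfer, and a null or adverse-looking result would not show that it fails to.

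The direction of the problem follows from the design. Its size does not. The 7–41% range for 20% more transfers depends on assumed transfer rates, severity gradients, a 1-sided 5% level and no clustering. A cluster-adjusted test would usually have a larger variance, which would pull these rates toward nominal but leave the spurious difference in place. The simulation also implies high event rates: 387 events among about 464 transfers (83%) in the central setting. The hand calculation at 40% risk shows the same direction, but its 31% is one point on assumed inputs and should not be read as the expected error rate. At 1-sided 2.5% it is 21%, the same as 2-sided 5%, so the part due to sidedness depends on the missing level.

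This should be corrected, but it does not threaten the primary analysis.

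**What to change.** Make the confirmatory secondary comparison one of all admissions: time from the first study room to the first event on the Hypothesis 2 list in Textbox 1, wherever it occurs. Deaths, arrests and intubations on the ward without ICU transfer count as events, and only patients with none of the listed events are event-free. Keep the whole list, or give a reason for any event dropped. Apply the primary's censoring for nonemergent transfers and bed changes, and state that emergent ICU transfer does not censor, since later events must be counted. Use a 2-sided cluster-adjusted test at the primary's level.

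A simpler alternative is to rely on the whole-stay proportions already listed, tested 2-sided.

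Keep the post-ICU curve among transferred patients as descriptive. Treat the outcomes restricted to sepsis-2 or never-transferred patients in the same way, read beside the all-admission septic shock, death and hospital length-of-stay outcomes.

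The cost is more than analysis-plan wording, because the hypothesis itself changes from the course after transfer to severe events in all admissions. The event rate per patient analysed falls. Two-sided testing also needs more events for 80% power at 5%: by 4(z_α + z_β)²/(ln HR)², 380 rather than 299 at a hazard ratio of 0.75, and 631 rather than 497 at 0.80. Little new data collection should be needed, since most of the listed events are already recorded over the whole hospital stay.

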#### Tertiary Hypothesis

The tertiary hypothesis is that the display of predictive analytics monitoring shortens time to proactive clinical response. We will quantify hours to proactive clinical response using variables found in Textbox 1.

We will use a Cox proportional hazards regression curve to determine differences in response time between intervention and usual care. We will also collect and analyze end points to evaluate clinician response and elements of situational awareness, including the number of alerts observed (per patient days) and clinical actions chosen (both individual actions or team/communication actions). By characterizing the clinical actions, we will be able to more fully understand the outcomes of dynamic decision making in the context of a predictive analytic and future state of disease. We will also be able to assess fidelity to the clinical guidelines that were provided to clinicians as a component of the optimized alert strategy.

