## Methods

### Overall Design

We will be conducting a parallel, cluster randomized controlled trial (RCT). All patients who are admitted to an 85-bed acute care cardiology medical-surgical floor will be enrolled in the study. In June 2020, institutional review board approval was granted for the Predictive Monitoring-Impact in Acute Care Cardiology Trial (PM-IMPACCT) along with waiver of informed consent, given the minimal risk nature of the study protocol. Clusters will be defined by room number, and upon enrollment, patients will be assigned to either intervention (CoMET display) or usual care (standard of care). The intervention will consist of CoMET display and charting in electronic medical records, mention of CoMET score on rounds, and standard of care cardiorespiratory monitoring when ordered. Meanwhile, usual care will consist of standard of care cardiorespiratory monitoring when ordered and no CoMET score displayed, charted, or mentioned on rounds. The study period will be 20 months. This report follows the SPIRIT (Standard Protocol Items: Recommendations for Interventional Trials) reporting guideline [24].

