#### Sample Size, Power Analysis, and Attrition

We expect 11% of participants to drop out of the primary outcome because they will be in a room that switches the randomization arm at the time when rooms are rerandomized or because they will transfer rooms during their admission to a room of the opposite randomization or to a nonstudy room. We have accounted for this attrition in clinical trial planning and sample size considerations. The number of admissions to a room which will undergo cluster randomization is estimated to be 10,424. The study type 1 error rate will be set to 5% and the type II error rate to 20% (80% power). Additionally, an interim analysis will prespecified after half of the participants have completed their primary outcomes assessment. The interim analysis will use an O’Brien-Fleming spending function, giving nominal α values of .003 (interim) and .047 (final) for the 2 analyses. Should the primary outcome cross a stopping boundary at the interim analysis, the data safety monitoring board (DSMB) will have the option of stopping the study early.

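### The tertiary time-to-response comparison names a Cox regression with no provision for clustering, although arm is assigned to room clusters in 2-month blocks

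*Protocol article*

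**What the plan says.** Under Randomization Process: "There will be 14 clusters containing an average of 4 rooms (6 beds) each". The same section adds: "Clusters will be rerandomized every 2 months following a replicated Latin square design within each stratum to ensure balanced treatment assignment within each time period". Under Overall Design: "The study period will be 20 months". The unit of assignment is therefore a room cluster for a 2-month period, not an admission.

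The article states how the correlation is handled in its other clinical comparisons:

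- **Primary outcome:** a GEE, chosen partly because it can deal with several levels of correlation.
- **Secondary survival outcome:** Kaplan-Meier or Cox curves display the result, and the comparison itself is a clustered log-rank test.
- **Secondary proportions:** GEEs, because "GEEs will allow the correct modeling of the clustering design and estimation of the intracluster correlation".

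Under Tertiary Hypothesis the Cox model is itself the comparison: "We will use a Cox proportional hazards regression curve to determine differences in response time between intervention and usual care". No cluster, period or stratum term, frailty or robust variance is mentioned. The outcomes box lists seven time-to-response endpoints for this hypothesis.

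**The concern.** The default variance of a Cox model assumes that admissions are independent given the covariates. Admissions to the same few rooms in the same 2 months share staff, rounding teams, ordering habits and case mix, and they share the arm. If these shared influences vary from one cluster-period to the next, the independent-admission standard error is too small.

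At stake is the claim that the display speeds clinical response, which is the mechanism by which it is meant to help. A test with understated standard errors could support that claim when the display has no effect. The contrast with the secondary survival outcome makes the gap visible: there the article goes beyond the Cox curve to a clustered test, and here it does not.

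**Working it through.** **Inputs from the document.** 14 clusters; rerandomization every 2 months; 20 months; 10,424 admissions ("The number of admissions to a room which will undergo cluster randomization is estimated to be 10,424"); 11% attrition, stated for the primary outcome ("We expect 11% of participants to drop out of the primary outcome"). The 10,424 cannot be re-derived, because no effect size, event rate, standard deviation or ICC is given; it is presented as an estimate of admissions.

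**Assumed inputs.** ICC, share of the correlation that persists across periods (cluster autocorrelation, CAC), frailty variance and event shares. The yardstick is a two-sided 5% test, because neither an alpha nor sidedness is stated for the tertiary tests.

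**Layout.** 20/2 = 10 periods; 14 x 10 = 140 cluster-periods; m = 10,424/140 = 74.5 admissions each. After 11% attrition, m = 9,277/140 = 66.3.

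**Formula.** Let rho be the correlation within a cluster-period. Each cluster rotates through both arms in balance, so the persistent part cancels:

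DE = 1 + (m - 1) x rho - m x CAC x rho

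Actual error of the unadjusted test = 2 x [1 - Phi(1.96/sqrt(DE))]

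Worked example, m = 74.5 and rho = 0.01:
- CAC = 0: DE = 1 + 73.5 x 0.01 = 1.735, error 13.7%.
- CAC = 0.8: DE = 1.735 - 74.5 x 0.8 x 0.01 = 1.139, error 6.6%.

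| ICC (rho) | CAC = 0 | CAC = 0.8 | CAC = 1 |
|---|---|---|---|
| 0.002 | 6.7% | 5.3% | 5.0% |
| 0.005 | 9.4% | 5.8% | 4.9% |
| 0.01 | 13.7% | 6.6% | 4.9% |
| 0.02 | 21.2% | 8.3% | 4.8% |

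The CAC = 0 column is the worst case. With m = 66.3 it is slightly lower (12.7% at 0.01 and 19.7% at 0.02).

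**When the error doubles.** An error of 10% needs DE = (1.96/1.645)^2 = 1.42. At m = 74.5 to 66.3 that is an ICC of 0.0057 to 0.0064 if CAC = 0, 0.012 to 0.013 if CAC = 0.5, and 0.030 to 0.034 if CAC = 0.8. It is never reached if CAC = 1.

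**Dependence on event frequency.** For a Cox test with period-specific frailty variance theta, DE is about 1 + theta x (events per cluster-period). At 66.3 admissions per block, reaching 10% error needs theta of about 0.32 if 2% of admissions have the event, 0.13 at 5%, 0.063 at 10% and 0.021 at 30%.

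**Simulation.** Unadjusted log-rank (Cox score) test with no treatment effect; 14 clusters x 10 periods; 7 clusters per arm in each period and 5 periods per arm in each cluster; 66 admissions per block; 1,500 replicates. Rejection rates:

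| Assumed event share | No clustering | Persistent cluster variance 0.10 only | Cluster-period variance 0.05 | Cluster-period variance 0.10 |
|---|---|---|---|---|
| 3% | 4.7% | 5.4% | 5.2% | 7.5% |
| 10% | 5.7% | 4.2% | 8.4% | 12.5% |
| 30% | 5.1% | 4.5% | 15.6% | 27.1% |

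The Monte Carlo standard error near 5% is sqrt(0.05 x 0.95/1,500) = 0.6 percentage points, so the first two result columns are compatible with 5%.

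**The case against.** The strongest reply is that the defect is read from silence. The article does not call the Cox model unadjusted or say that admissions are treated as independent. Robust variance, frailty and stratification are all ways to fit a Cox model, a condensed article may leave the choice to the analysis plan, and the authors plainly know that clustering matters. This stands as a limit: a correction may exist in the plan that is not shown. It does not dispose of the point. The article does specify the handling of clustering for the primary and secondary comparisons, and for the secondary survival outcome it names a separate clustered test. The tertiary section makes the Cox regression the test and names nothing further, so the method as stated does not fit the design.

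The second reply is that the rotation protects the comparison. This is right for stable room and ward differences, and the simulation confirms it. It does not cover influences that change between cluster-periods.

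A reader might infer that all seven tests run at two or more times the nominal error. The document does not support that. It gives no ICC, no autocorrelation and no event rates. Doubling requires an assumed period-specific ICC of about 0.006 or more, and endpoints occurring in about 2-3% of admissions stay near 5-7.5% in the scenarios tried.

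Finally, this is the tertiary hypothesis. The 5% in the sample-size section is the study error rate, and no alpha is assigned to these tests.

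**Conclusion.** The point holds in a conditional form. As written, the tertiary comparison names a method that does not reflect how arm was assigned and departs from what the article does for its first two hypotheses. With independent-admission variance it is anti-conservative whenever there is correlation within a cluster-period beyond the persistent room effects.

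Under assumed ICCs of 0.002 to 0.02, the actual error of a nominal 5% test runs from about 7% to 21% if the correlation is entirely period-specific. If 80% of it persists, the error is about 7-8% at ICCs of 0.01 to 0.02. If all of it persists, there is no inflation. Frequently ordered endpoints carry most of the risk. The primary conclusion and the interim stopping rule are not affected. The change is worth making before analysis because it is cheap and protects the claim about mechanism.

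**What to change.** In Tertiary Hypothesis, specify that the Cox comparisons account for cluster and period, in line with the primary and secondary analyses. For example, use a Cox model stratified by randomization stratum and 2-month period, with one of:

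- a cluster-robust variance with a small-sample correction for 14 clusters; or
- a p-value from re-drawing the Latin-square assignments within strata.

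Either would serve; the choice should be fixed in advance and applied to all seven endpoints. In a separate simulation of two scenarios with generically balanced re-draws, the re-draw test rejected in 5.7% and 4.1% of runs. That did not reproduce the stratified Latin square, so the check should be repeated with the actual scheme.

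The cost is a sentence in the plan and a few lines of code, with no new data. The downside is somewhat wider confidence intervals for the tertiary endpoints.

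### The Hypothesis 3 hazard ratio mixes whether an order is placed with when, so a ratio above 1 does not by itself show a shorter response time

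*Protocol article*

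**What the plan says.** The Tertiary Hypothesis section makes a claim about timing, that "the display of predictive analytics monitoring shortens time to proactive clinical response". It names the model and its purpose together: "We will use a Cox proportional hazards regression curve to determine differences in response time between intervention and usual care".

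Textbox 1 (Hypotheses 3 and 4) lists seven endpoints. Six are times to a first order, such as "Time to first order for blood or urine culture obtained for suspicion of infection" and "Time to first order for lactate drawn". The seventh is time to a rapid response call. The list names no subset of patients who needed a response. The Overall Design section says "All patients who are admitted to an 85-bed acute care cardiology medical-surgical floor will be enrolled in the study".

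The section on implementation and education for clinicians describes what staff may do when the score prompts them: "Clinicians may choose to draw a blood culture, initiate a rapid response team call", among other options. Both of these actions are Hypothesis 3 endpoints.

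For binary secondary outcomes the plan already has a method: "For secondary outcomes measured as proportions (ie, yes-or-no outcomes) we will use GEEs with logit link and binomial distribution".

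**The concern.** Some patients may never receive a given order. For a first-event endpoint of that kind, the hazard ratio rises if the same patients are treated sooner. It also rises if more patients are treated and nobody is treated sooner. The article reads the ratio as a difference in response time, which is only the first of these.

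The second route is realistic here. The display is visible to staff, and drawing a culture or calling the rapid response team is offered as a possible reaction to it. A ratio above 1 could therefore be reported as faster response when the data show only that ordering became more common. For a tool meant to prompt earlier action these are different findings, with different implications for workload and for the proposed mechanism.

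**Working it through.** The article gives no ordering rate, hazard ratio or power for Hypothesis 3, so there is no figure of its own to reproduce. The question is whether the hazard ratio can move with timing held fixed, and by how much under stated assumptions.

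**Inputs from the article.** The section on sample size, power and attrition gives 10,424 admissions and 11% attrition. The attrition is stated for the primary outcome and is carried over here as an assumption. Then 10,424 × 0.89 / 2 ≈ 4,638 per arm.

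**Assumed inputs.** Usual-care ordering p0 of 10%, 20% or 30%; one or two extra percentage points with the display (p1); two-sided 5% test; design effect (deff) of 1 or 2.

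**Formulas, timing unchanged.**
- HR ≈ ln(1 − p1) / ln(1 − p0)
- z = ln(HR) / √[deff × (1/(N·p0) + 1/(N·p1))]
- power = P(Z > 1.96 − z)

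For 10% v 12%: HR = ln(0.88)/ln(0.90) = 1.21. The expected numbers ordered are about 464 and 557, so z = 3.08 and power = 87%.

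| p0 → p1 | HR | z | Significant, deff 1 | Significant, deff 2 |
|---|---|---|---|---|
| 10 → 11% | 1.11 | 1.57 | 35% | 20% |
| 20 → 21% | 1.06 | 1.20 | 22% | 13% |
| 30 → 31% | 1.04 | 1.05 | 18% | 11% |
| 10 → 12% | 1.21 | 3.08 | 87% | 58% |
| 20 → 22% | 1.11 | 2.37 | 66% | 39% |
| 30 → 32% | 1.08 | 2.09 | 55% | 32% |

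**Check by fitted Cox model.** This simulation used 9,277 admissions, log-normal stay with median 96 h capped at 504 h, the same order-time distribution in both arms, never-ordered patients censored at end of stay, 200 runs per scenario and no clustering.
- 10% v 10%, same timing: HR 0.99, 4% rejections in total.
- 10% v 12%, same timing: HR 1.22, significant in 85%; median time among ordered patients about 25 h in both arms.
- 10% v 10%, orders 25% earlier with the display: median 25.3 h v 18.9 h, yet HR 1.00 and significantly faster in 2.5%.
- 10% v 8%, orders 25% earlier with the display: HR 0.79, significantly slower in 94%.

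**Does this depend on starting the clock at admission?** A second simulation started follow-up at a score rise. It assumed that 20% of admissions alert (928 per arm), a 48 h window, exponential response times truncated at 48 h with mean parameter 12 h, 600 runs and no clustering.

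| Change with the display | 30% ordered | 50% ordered | 70% ordered |
|---|---|---|---|
| +2 points, same timing | HR 1.08 (13% significant) | 1.06 (14%) | 1.05 (12%) |
| +5 points, same timing | 1.20 (61%) | 1.14 (52%) | 1.13 (61%) |
| Same proportion, mean parameter 12 h → 6 h | 1.06 (10%) | 1.12 (41%) | 1.22 (94%) |

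In the rows with unchanged timing the median time to order was 8.1 h in both arms. The mixing is present under either origin. What depends on the origin and the ordering rate is how well the ratio also picks up a true speed-up.

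**The case against.** The strongest reply is that the Cox analysis is sound as it stands. Over all randomized patients, if more have an order by every time point, time to response is stochastically shorter. A patient who would have had no order and now has one has, on that view, been responded to sooner. Holding timing fixed means conditioning on having received an order, a post-randomization event that the display may alter. That comparison is not protected by randomization. This stands: the Cox analysis addresses a legitimate estimand, and a reader who inferred that the model is wrong would go further than the article supports. What remains is that the article calls the result a difference in response time and does not say that a new order counts as a faster one.

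A second reply is that risk set, time origin and censoring belong in the analysis plan, which is not shown. That is also right, and their absence from an article is no fault. The point does not need them, since the mixing appears under both origins tried.

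Third, part of the safeguard is already planned. Clinical actions chosen are to be analysed. Proportions are listed for large transfusions and for inotrope or vasopressor use, and days on antibiotics and anti-infectives are counted. Table 1 includes the cost of unnecessary intervention. Culture, anti-infective and fluid orders count only when infection or shock is suspected. These help, but none is tied to the reading of the hazard ratio. The listed proportions omit cultures, lactate, anti-infectives, fluids and rapid response calls.

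Finally, the larger figures need two extra points across all admissions. If every extra order came from an alerting 20%, that would be 2 / 0.20 = 10 points among them. Five points among alerters is only 5 × 0.20 = 1 point overall, where the chance of significance is 35/22/18%, or 20/13/11% with a design effect of 2.

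**Conclusion.** The concern holds as one of interpretation. A hazard ratio above 1 for time to first order does not by itself show that the display shortens response time, because more frequent ordering with unchanged timing among those ordered produces the same result. That follows from how the measure works and does not depend on the assumed rates.

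The size does depend on them. Under the all-admissions assumptions, one to two extra points give hazard ratios from 1.04 to 1.21. The chance of significance runs from 18% to 87% without clustering and from 11% to 58% with a design effect of 2. Ordering rates, stay, order timing, alert share and design effects are all assumed, so these figures are illustrations and not forecasts.

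A reader might infer that the trial will report a false speed-up, or that extra orders would be unneeded. The article supports neither: it gives no data on ordering, and an extra order may be a proper response. The matter concerns a tertiary hypothesis and leaves the primary outcome, the stopping rule and the sample size untouched. It is a low-priority change that is cheap to make.

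**What to change.** Keep the Cox model and describe its hazard ratio as a rate of first orders. Then:

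- For cultures, lactate, anti-infectives, fluids and rapid response calls, report by arm the proportion with any such order or call, using the logit-link GEE already planned for binary secondary outcomes. Use the same follow-up window and censoring rule as the Cox model, for example up to a bed change. Whole-stay proportions would include time after a move, when allocation can switch; the primary outcome is censored at transfer for that reason.
- Show cumulative incidence curves by arm, with discharge, death and ICU transfer as competing events.
- State the reading rule in advance. If both the proportion and the hazard ratio are higher with the display, report more frequent and/or earlier ordering. Claim earlier response only when the curves separate early and the end-of-window proportions are similar.
- Label any comparison of times among ordered patients as descriptive, because it conditions on a post-randomization event.

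The cost is a few table rows and curves from order timestamps that the time-to-order endpoints already require, a short statement on interpretation, and a more cautious tertiary conclusion. Design, endpoints and sample size do not change.
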